#### Analysis of secondary outcomes

Outcomes 2 and 3 are rates of ED transfers and hospital admissions and will be investigated using a mixed-effects Poisson regression model. The offset or exposure variable will be the number of resident days, and outcomes expressed as rates per 1000 resident days. The covariates included will be a temporal indicator for the baseline phase to the intervention exposure phase switch to estimate the change associated with the EDDIE+ intervention, calendar time in months, mode of arrival, and random intercept term for each RAC facility.

Outcome 4 is admitted patient length of stay and will be analysed using a mixed-effects Gamma regression model. The covariates included will be a temporal indicator for the baseline phase to the intervention exposure phase switch to estimate the change in average length of hospital stay associated with the EDDIE+ intervention period, calendar time in months, resident age, resident sex, mode of arrival, and random deviations for each RAC facility from the overall pre-intervention average length of hospital stay.

Outcome 5 is family awareness and experience of EDDIE+ and will be investigated using a short questionnaire (Additional file 2) as well as semi-structured qualitative interviews conducted at the end of the trial period. Questionnaire responses will be summarised using descriptive statistics. Interview transcripts will be analysed and reviewed by two experienced qualitative researchers using NVivo software, and an inductive thematic analysis approach [21]. Concurrent analysis of interviews will iteratively inform subsequent interviews until saturation [22]. Illustrative quotes will be used to support the themes generated.

Outcome 6 is staff self-efficacy and will be measured through a validated questionnaire [19] administered to all nursing staff and personal care workers via a questionnaire at the commencement of the intervention introduction phase and at the end of the trial period. Separate analyses will be performed for the job-related self-efficacy questions and group-related self-efficacy questions. Internal consistency of the questionnaire will be assessed using the appropriate test statistic as determined by the distributions of the questionnaire items and total scores [23]. Difference between the average scores in the baseline and intervention exposure phases will be assessed using a *t*-test to obtain an overall change in staff’s self-efficacy before and after the intervention. Additionally, we will perform a linear regression analysis to investigate the potential contribution of different staff-related factors in the change in job-related self-efficacy average scores reported by staff between the baseline and intervention exposure phases. Relevant staff-related factors might include age, sex, staff role, years of experience in working in RAC facility, and RAC facility.

Outcome 7 is the cost of implementing the intervention and will be measured by valuing the costs of any materials, equipment and activities required as part of the intervention introduction and exposure phases. The duration of RAC home and project staff time associated with implementation activities, including training and attending meetings or other program-related activities, will be collected using prospective weekly activity logs completed by the EDDIE+ Nurse Educator and local EDDIE+ facilitators, to record minutes of staff time and grade of nursing staff and personal care workers. The economic opportunity costs of staff time will be valued using relevant wage rates plus on-costs to account for the full costs of employment. Quantities and types of consumables and incidentals used will be recorded and valued in monetary terms using market prices. The key outcome will be the estimated total cost of implementing the EDDIE+ intervention. Uncertainty will be represented using bootstrapped 95% confidence intervals.

Cost data on the health services used by residents during the trial will be retrieved from a state-level hospital costing database. These data will provide direct and overhead costs for each resident ED presentation and hospital admission. Statistical distributions will be used to describe variability in all cost items. The normal, uniform, beta and gamma distributions will be used depending on the type of parameter. Fitted distributions will be randomly re-sampled and the economic outcome of ‘change to total costs’ (outcome 8) simulated 10,000 times. This approach propagates uncertainty in prior parameters forward to the total cost outcomes. The key output will be the average cost per resident together with 95% bootstrap confidence intervals to estimate the uncertainty in this average.

Further details on planned residual checks and sensitivity analyses are included in Additional file 3.

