**Effectiveness outcomes**		
Primary outcome (Outcome 1)	Number of hospital bed days	Total number of hospital bed days residents accrued during the baseline and intervention exposure periods, accounting for RAC home occupancy levels.
Outcome 2	Emergency Department (ED) transfer rates	Resident transfers to emergency departments including mode of transfer, diagnosis code, triage category, length of stay (mins) and discharge outcome.
Outcome 3	Hospital admission rates	Residents admitted to hospital as an inpatient (exclusive of dialysis admissions) including diagnosis code (Australian Refined Diagnosis Related Group (AR-DRG)) and mode of arrival.
Outcome 4	Length of hospital stay and discharge outcome	Time (in days/hours) from admission to discharge for each episode of care including diagnosis code, time in intensive care unit and discharge outcomes.
Outcome 5	Family awareness and experience	Family or nominated advocate responses to a short questionnaire and/or interview to ascertain awareness of EDDIE+ and family perceptions and experiences of the program.
Outcome 6	Staff self-efficacy	Staff scores on the Job-related and Group-related Self-Efficacy measure [19]

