### Analysis

The time unit used in the analyses of Outcomes 1 to 4 is months. Data from the intervention introduction phase (phase 3) will not be in included in the statistical analyses but will instead inform the process evaluation. Subgroup analyses of Outcomes 1 to 6 will be performed for each RAC home separately. An initial analysis will be created using a scrambled intervention group by randomly allocating each RAC home to the baseline or intervention exposure period. A complete statistical report will be created using this scrambled data and sent to all investigators for discussion. This will allow investigators to query the methods and approaches used prior to the final report. It can also uncover errors in the code or data. Changes can be made prior to seeing the main results, which will help avoid the bias of only making changes where results are perceived as unfavourable.

There is a possibility that a disease outbreak (including COVID-19) could occur in one or more of the enrolled RAC homes during the study period. This may impact on hospital transfers and admissions and could potentially bias primary and secondary outcome findings. The analysis of Outcomes 1, 2, 3, 4 and 8 will therefore be conducted both with and without the inclusion of any outbreak related transfers and admissions.

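### Outcomes 2 and 3: the resident-day rate models adjust for mode of arrival, which exists only where an event occurred; in Outcome 4 it is a post-exposure covariate; and the Poisson models have no within-home dispersion term

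*Protocol article*

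**What the plan says.** Under Analysis of secondary outcomes, Outcomes 2 and 3 "will be investigated using a mixed-effects Poisson regression model". On exposure the article says: "The offset or exposure variable will be the number of resident days, and outcomes expressed as rates per 1000 resident days". The covariates are the phase indicator plus "calendar time in months, mode of arrival, and random intercept term for each RAC facility".

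Outcome 4 has a different model: "Outcome 4 is admitted patient length of stay and will be analysed using a mixed-effects Gamma regression model". Besides the phase indicator it adjusts for "calendar time in months, resident age, resident sex, mode of arrival, and random deviations for each RAC facility".

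The Analysis section adds: "The time unit used in the analyses of Outcomes 1 to 4 is months".

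Table 1 (Effectiveness outcomes) shows the level at which mode is recorded. For Outcome 2 the measure is "Resident transfers to emergency departments including mode of transfer, diagnosis code, triage category, length of stay (mins) and discharge outcome". For Outcome 3 it covers inpatient admissions, "including diagnosis code (Australian Refined Diagnosis Related Group (AR-DRG)) and mode of arrival". In both, mode is an attribute of an event and is listed as part of the outcome measure.

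The article names no dispersion parameter or alternative to Poisson. It refers residual checks and sensitivity analyses to Additional file 3, which is not shown.

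**The concern.** There are three separate issues, and they do not all apply to the same outcomes.

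- **Outcomes 2 and 3, definition.** A rate model needs each covariate to have a value for the exposure in the offset. A resident day on which nobody was transferred has no mode of arrival, so it cannot be assigned to a level of that covariate. The analyst must choose a layout, and the choice can change the answer.
- **Outcome 4, post-exposure adjustment.** Every admission has a mode, so the model can be fitted. But mode is fixed only when the resident is sent to hospital. A programme built on earlier detection and proactive management could plausibly alter it. Conditioning on it may take out or distort part of the effect on length of stay. Age and sex, also listed, do not share this problem.
- **Outcomes 2 and 3, variance.** The home random intercept absorbs stable differences between homes. It is constant over time, so it does not absorb repeat transfers of the same resident or clusters of events within a month.

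At stake are the estimates and intervals for the secondary utilisation outcomes.

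**Working it through.** **Figures in the plan.** The article gives no event rate, variance or power for Outcomes 2 to 4. Its 91% power is for bed days and does not bear on this point. It cannot be reproduced in any case, because no bed-day variance is given.

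**1. How much exposure has no mode?** Inputs: 346 bed days per 100 residents per year and 100 residents per home (Sample size calculation); about 160,000 bed days for 27,000 potentially preventable admissions (Background). Assumption: that average stay applies here.

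- Stay: 160,000 / 27,000 = 5.93 days.
- Admissions: 346 / 5.93 = 58.4 per 100 residents per year, or 58.4 / 12 = 4.87 per home-month.
- Resident-months without an admission: exp(−4.87/100) = 95%. Home-months without one: exp(−4.87) = 0.8%.

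So almost every home-month has some event, but most resident exposure carries no mode.

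**2. Layout A: counts by home, month and mode, zeros filled.** With main effects only and the same offset in each mode row, the home-month total has mean Σ exp(η + γ_k) = exp(η) × Σ exp(γ_k), where γ_k is the effect of mode k. The mode terms only shift the intercept, so the phase coefficient is unchanged. Simulation agrees: rate ratios with and without mode were 0.803 and 0.803, 0.758 and 0.758, 0.726 and 0.726.

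**3. Layout B: monthly share by mode as a covariate.** In the same three settings the ratios were 0.804, 0.757 and 0.730, so there is little movement. The share is undefined in an empty home-month.

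**4. Layout C: rows exist only where an event occurred.** Assumptions: 6 events per home-month, 5.5 in a common mode and 0.5 in a rare one; true ratio 0.59 in both. The 0.59 is 1 − 0.41, borrowed from the bed-day effect in the sample size section. A cell with mean λ yields a row with probability 1 − exp(−λ), and the row mean is λ / (1 − exp(−λ)).

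| Mode, phase | λ | P(row) | Row mean |
|---|---|---|---|
| Common, baseline | 5.5 | 0.996 | 5.52 |
| Common, intervention | 3.245 | 0.961 | 3.38 |
| Rare, baseline | 0.5 | 0.393 | 1.27 |
| Rare, intervention | 0.295 | 0.255 | 1.155 |

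Within-mode ratios are 3.38/5.52 = 0.61 and 1.155/1.27 = 0.91. The plan has one phase coefficient and no phase-by-mode term. Fitting that Poisson model to these rows, weighted by P(row), gives fitted means of 5.458 and 3.443 (common) and 1.433 and 0.904 (rare).

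- Check on totals, baseline: 0.996 × 5.458 + 0.393 × 1.433 = 6.00.
- Check on totals, intervention: 0.961 × 3.443 + 0.255 × 0.904 = 3.54 = 6 × 0.59.
- Pooled ratio: 3.443 / 5.458 = **0.63**.

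With a 5/1 split of the 6 events the pooled ratio is 0.65. In a denser simulated case (10 events per month, 80/20 split, true 0.80 in both modes) it was 0.815. When the simulated effect differed between modes the shift was negligible (0.759 against 0.758, and 0.723 against 0.726, without mode).

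**5. Overdispersion.** Let φ be the within-home-month variance/mean ratio; the documents give none. If the Poisson standard error is too small by 1/√φ, the two-sided error at nominal 5% is 2(1 − Φ(1.96/√φ)). Simulated values are from a Poisson random-intercept model on null data (12 homes, 13 months, mean 4.87 or 10 events, 600 runs each).

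| φ | Formula | Simulated | Model SE / true SD |
|---|---|---|---|
| 1 | 5.0% | 5.5–5.8% | 0.96–0.98 |
| 1.25 | 8.0% | 7.7–9.3% | 0.85–0.91 |
| 1.5 | 11.0% | 10.2–11.3% | 0.82–0.83 |
| 2 | 16.6% | 15.0–15.7% | 0.71–0.72 |
| 3 | 25.8% | 23.5–26.3% | 0.57–0.60 |

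A second set (6 events per month, 1,500 null runs per scenario, home effects and linear time) gave 11.9 to 12.7% at φ of about 1.6 and 22.8 to 25.9% at 2.2 to 2.9. Scaling for dispersion brought these to 4.4 to 5.9%.

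**The case against.** The strongest reply has four parts.

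- **Layout.** A journal article commonly leaves data structure to the full plan, and nothing says empty cells will be dropped. The zero-filled layout makes the models well defined and the covariate harmless. That stands, and it limits the expected damage. It does not defend the covariate, which then contributes nothing to the intervention estimate.
- **Size.** A reader might infer from the rare-mode figure that a true 0.59 would be reported as 0.91. The planned model does not support that: 0.91 is the ratio inside one sparse mode, while the single phase coefficient is about 0.63. The 0.59 itself is a bed-day effect, combining transfers and length of stay, and the article offers no such effect for rates.
- **Variance.** A reader might infer that the intervals for Outcomes 2 and 3 are too narrow. No document figure shows it. At φ = 1 there is no material problem, outbreak-related events are also analysed by exclusion, and Additional file 3 may contain a dispersion check. So this part must stay conditional. Excluding outbreaks does not deal with repeat transfers or other monthly clustering.
- **Outcome 4.** A reader might extend the definition and Poisson arguments to length of stay. Neither applies: it is a Gamma model on admissions, each with a mode. Nor is mode always measured after crossover, since baseline admissions have one too. What remains is that mode is post-exposure. The article does not say that the programme changes it, and the effect of adjusting is not quantified.

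**Conclusion.** The point holds as a should-fix on secondary outcomes.

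- **Outcomes 2 and 3:** mode of arrival has no value for event-free exposure, so the models are incomplete as written. The effect on the rate ratio ranges from none (zeros filled) to a modest pull towards 1 (0.63 against 0.59 on assumed counts, an assumed effect common to both modes, and lost empty cells).
- **Outcome 4:** adjustment for mode may remove or distort part of the effect. The direction and size are unknown.
- **Poisson variance:** if counts are overdispersed, type I error would be about 10 to 13% at φ of 1.5 to 1.6 and 15 to 26% at φ of 2 to 3. Repeat transfers and outbreaks make this plausible, but φ is an assumption throughout.

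A reader might infer that the trial's main result is at risk. It is not: the primary model for bed days contains neither mode of arrival nor a Poisson variance.

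**What to change.** 1. Delete mode of arrival from the models for Outcomes 2 and 3 and from the main model for Outcome 4. Report rates and lengths of stay by mode as a descriptive breakdown.
2. Fit Outcomes 2 and 3 with a mixed-effects negative binomial model and the same resident-days offset, or keep Poisson with a dispersion-robust variance, unless Additional file 3 already provides for this.

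The cost is a change of analysis wording and, where counts are overdispersed, slightly wider intervals. No data collection changes. The article already plans a full report on scrambled allocation before the real results are seen, so the change can be made and checked at that stage.

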### Setting and participants

The trial will be undertaken at 12 RAC homes in Queensland, Australia. Data will be collected from five participant groups:
RAC homes will be enrolled in the study as the main participant group. For inclusion, the RAC homes must be located in Queensland and be operated by the study partner, Bolton Clarke, a not-for-profit aged care provider. We will purposively sample from 21 eligible homes to ensure the program is implemented across a range of regional and metropolitan settings. A lower priority will be placed on homes with existing locally implemented hospital avoidance programs to minimise potential confounding with our study intervention. A lower priority will also be placed on homes with lower bed numbers to minimise the risk of underpowering the study.All nursing staff and personal care workers at each enrolled RAC home will participate in the study, with no exclusion criteria.Data on all residents at each enrolled RAC home will be collected as part of the study, with no exclusion criteria. A waiver of consent has been granted for resident data collection in recognition of the low privacy risk and negligible participant burden, as data will be de-identified and obtained indirectly from routinely collected databases and chart notes.All family members or nominated advocates of residents at each enrolled RAC home will be invited to participate in the study, with no exclusion criteria.A purposive sample of key internal and external stakeholders at each enrolled RAC home will be invited to participate in the study, with no exclusion criteria.

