### Sample size calculation

A simulation-based statistical power calculation was performed for the primary outcome of total hospital bed days. The simulations used a stepped-wedge design of 12 sites of 100 residents per site with 1 site switched from baseline phase to intervention exposure phase each month as shown in Fig. 1. The study design was estimated to have a 91% power to detect a 41% reduction in total bed days from a baseline period total hospital bed days of 346 bed days per 100 residents per year [12]. The power calculation was based on a 5% statistical significance level.

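### The length-of-stay model (Outcome 4) has no resident term, so repeat stays count as independent given the home: its standard error can be slightly too small, and a little precision is lost

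*Protocol article*

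**What the plan says.** Table 1 of the protocol article defines Outcome 4 stay by stay: "Time (in days/hours) from admission to discharge for each episode of care". The Setting and participants section does not restrict who contributes: "Data on all residents at each enrolled RAC home will be collected as part of the study, with no exclusion criteria". A resident admitted three times therefore supplies three observations.

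The section Analysis of secondary outcomes names the model: "Outcome 4 is admitted patient length of stay and will be analysed using a mixed-effects Gamma regression model". Its listed terms are the phase switch, calendar month, and "resident age, resident sex, mode of arrival, and random deviations for each RAC facility from the overall pre-intervention average length of hospital stay". Resident age and sex are covariates, so the unit of analysis is the single stay. The article names no resident random effect, no variance clustered on resident, and no rule limiting a resident to one stay.

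**The concern.** Stays of the same resident are likely to be alike in length, because frailty, comorbidity and goals of care carry over. The listed model allows for likeness within a home but not within a resident. Two things can follow. The reported standard error of the intervention effect may not match its true sampling error, and the analysis may use the data less efficiently than it could.

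The stake is modest but real. The Background reports that the pilot lowered both transfer rates and average stay, and so cut bed days by 41%. The Outcome 4 result will therefore be read as part of the explanation of the primary result.

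**Working it through.** The article has no figure to reproduce here. Its 91% power concerns total bed days, and it states no precision for Outcome 4.

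**Step 1: how many stays.** The Background gives 160,000 bed days for 27,000 potentially preventable admissions, or 160,000 / 27,000 = 5.93 days per stay. Using this as the mean stay is an assumption. The Sample size calculation gives 346 bed days per 100 residents per year, so 3.46 / 5.93 = 0.584 admissions per resident-year. The design there is "12 sites of 100 residents per site with 1 site switched from baseline phase to intervention exposure phase each month". The 58 weeks are about 13 months. If one month per home is dropped for the introduction phase (assumed), 12 months remain: 1,200 × 0.584 × 1 = about 700 stays.

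**Step 2: the direction of the error.** Take a simplified two-phase comparison with n stays per phase and correlation ρ between stays of one resident. Let S be the number of same-resident pairs with both stays in one phase, and C the number with one stay in each phase. Then

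- variance assumed by the model: 2σ²/n
- true variance: (2σ²/n) × [1 + ρ(S − C)/n]
- model SE / true SE: r = 1 / √[1 + ρ(S − C)/n]

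If S = C, the error cancels. If S exceeds C, the SE is too small; if C exceeds S, it is too large. Quick readmission and resident turnover raise S. So does the exclusion rule, "Data from the intervention introduction phase (phase 3) will not be in included in the statistical analyses", because it removes stays around the switch, where a short-gap pair could straddle the two phases. For scale, take n = 350 and ρ = 0.3. Then r = 0.93 needs 1/0.93² − 1 = 0.156 = 0.3(S − C)/350, so S − C is about 182 pairs. The real design weights stays by home and month, so this shows direction only.

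**Step 3: size in the stepped wedge.** Log-scale variance calculations used 12 homes of 100 residents, one home switching per month and the introduction month dropped. The model had a home intercept, phase and linear month. All repeat-stay inputs are assumptions.

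- *No short-gap readmission.* Residents differ in admission proneness (frailty variance 1), turnover is 2% a month and within-resident correlation is 0.1 to 0.3. Some 56 to 61% of stays come from residents with more than one stay, and 23 to 29% from residents with stays in both phases. The ratio r is 0.93 to 0.97 with zero home variance (coverage of a nominal 95% interval 93.1 to 94.4%). With home variance at 0.1 to 0.5 of the stay variance it is 0.995 to 1.003 (coverage 94.9 to 95.1%).
- *Direct mixed-model fits under similar assumptions.* At correlation 0.3 the mean SE was 0.1228 against an empirical SD of 0.1248 (coverage 96.7%). At 0.5 it was 0.1238 against 0.119 (97.5%). With 120 replicates, the Monte Carlo error of coverage is √(0.95 × 0.05/120) = 2.0 points, so a loss of one or two points could not be seen.
- *Readmission probability 30%, mean gap 30 days, correlation 0.25.* The ratio is 0.949, 0.955 and 0.957 at home variance 0.02, 0.1 and 0.3. Here home variance does not remove the error.
- *Overall range.* With readmission 0 to 40%, correlation 0.15 to 0.3 and about 570 to 730 stays, r is 0.93 to 1.00.

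Type I error is 2[1 − Φ(1.96r)]. At r = 1.00 it is 5.0%. At r = 0.93, 1.96 × 0.93 = 1.823, which gives 6.8%.

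**Step 4: precision.** Over the same overall range, a resident term makes the SE 0.5 to 6% smaller. In variance that is 1 − 0.995² = 1.0% to 1 − 0.94² = 11.6%. It equals 1/0.995² = 1.01 to 1/0.94² = 1.13 times as many stays.

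**The case against.** The strongest defence is that homes cross over, so part of the within-resident correlation cancels, and that the randomised unit is already in the model. This stands in part: it is why the error is a few percent and can vanish. It does not stand where readmission soon follows discharge.

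A second defence is that such detail belongs elsewhere. The article sends residual checks and sensitivity analyses to Additional file 3, which is not shown, and it plans a dry run on scrambled data in which methods may change. But the article lists the terms of this model, and a sensitivity analysis would not alter the main model.

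A reader might also infer more than the documents support:

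- **That the intervals are too narrow as a fact.** The direction depends on home variance, timing of readmission and within-resident correlation, and the article gives none of them.
- **That the false-positive rate reaches 9 to 10.5%, or that a resident term is worth 29% more stays.** The first appeared only at an assumed 40% readmission after about 30 days. The second is one extreme setting (correlation 0.4 with 40% readmission).
- **That residents with many stays get too much weight.** The target is the average stay. Equal weight per stay suits that target, and mean stay times admissions gives bed days.

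**Conclusion.** The point holds as a minor one. The listed Outcome 4 model ignores correlation between stays of one resident. The standard error of the intervention effect is about 0 to 7% too small, with type I error about 5 to 7%, under assumed readmission of 0 to 40% and within-resident correlation of 0.15 to 0.3. It is near nominal when stays are spread out. About 0.5 to 6% of the standard error is lost as precision.

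These figures rest on assumed repeat-stay patterns, on a mean stay borrowed from national figures for preventable admissions, and on log-scale calculations rather than fits of the planned Gamma model. The outcome is secondary, and the primary analysis is not affected.

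**What to change.** In Analysis of secondary outcomes, add to the Outcome 4 model a random intercept for each resident, nested within RAC facility. State the fallback in advance: if that model does not converge, fit the 12 facilities as fixed effects and use standard errors clustered on resident. Clustering on resident while keeping a random facility term would not do, because residents who share a home effect are not independent clusters.

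The costs are:

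- One extra model term, with some risk of non-convergence because many residents will have only one stay. The article already foresees convergence trouble with a facility intercept alone for the primary outcome.
- A resident intercept gives relatively less weight to residents with many stays, so the estimate moves a little away from a plain average over stays. The fallback keeps equal weight per stay.
- The extraction must carry a de-identified resident key across stays. This should be confirmed: the section Health services use and cost data promises individual-level data but links the state records by home address. The Outcome 8 plan, "The key output will be the average cost per resident", does not settle it, since that average can be total cost divided by the number of residents.

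The scrambled-data report is a convenient point to make the change, before any results are seen.

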#### Staff self-efficacy questionnaire

All nursing staff and personal care workers staff will be invited to complete a baseline measure of occupational self-efficacy using a validated questionnaire [19] to be administered immediately prior to staff training sessions. The self-efficacy questionnaire will be repeated in the final 2 weeks of the intervention exposure phase and up to 2 weeks post implementation.

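### Staff self-efficacy (Outcome 6) is tested with a t-test of unstated pairing and no term for the 12 homes: its p-value is unreliable in either direction, and the result is an uncontrolled before-after change

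*Protocol article*

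**What the plan says.** In the protocol article, Analysis of secondary outcomes, the Outcome 6 text states: "Difference between the average scores in the baseline and intervention exposure phases will be assessed using a" *t*-test, in order to describe "self-efficacy before and after the intervention". The job-related and group-related scales are analysed separately. The text does not say paired or unpaired, and names neither a home term nor a time term for this test.

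On timing, the same section places the surveys "at the commencement of the intervention introduction phase and at the end of the trial period". Under Staff self-efficacy questionnaire, all nursing and personal care staff "will be invited to complete a baseline measure of occupational self-efficacy" immediately before training, and the questionnaire is "repeated in the final 2 weeks of the intervention exposure phase and up to 2 weeks post implementation".

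A second analysis follows: "Additionally, we will perform a linear regression analysis to investigate the potential contribution of different staff-related factors". It concerns the change in the job-related score only. On covariates it says: "Relevant staff-related factors might include age, sex, staff role, years of experience in working in RAC facility, and RAC facility". Calendar time is not listed.

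Outcomes 1 to 4 are each given a home-specific random term and a time term. Table 1 lists Outcome 6 among the effectiveness outcomes, and the Discussion names secular trends as a main drawback of the design.

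**The concern.** Two features of the data bear on the standard error, and they pull in opposite directions. Staff who answer twice give correlated scores; an unpaired test ignores this and is too cautious. Staff in one home share managers, training and local events, so a home's scores can move together between waves; either *t*-test ignores this and is too liberal. With the pairing unstated and no home term, a reader of the final report could not tell which error dominates.

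Timing raises a separate problem of meaning. Each home's baseline is taken at its own introduction date, while follow-up comes at the end of the trial. No home still on usual care is surveyed alongside homes that have the programme, so any drift in staff confidence over calendar time is added to the measured change. Because Table 1 counts Outcome 6 as effectiveness, a small p-value would readily be taken as evidence that EDDIE+ worked.

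**Working it through.** **No figure to reproduce.** The article gives no sample size, SD, intraclass correlation or staff number for Outcome 6.

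**Inputs from the article.** 12 homes; one home switched per month (Sample size calculation); two survey points per home. The 5% level is stated only for the primary outcome's power calculation and is assumed here.

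**Assumed inputs, not in the article.** Staff per home and wave m = 20 to 60; home intraclass correlation (ICC) 0.01 to 0.10; share of home variance that is stable across waves (CAC) 0.5 to 1.0; within-home correlation of a staff member's two scores 0.5; share of staff answering twice f = 0 to 1; last home followed for 2 months. Figure 1 is not shown, so the calendar layout is also assumed.

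**Variance parts (total 1).** Home-by-wave b = ICC × (1 − CAC); staff c = (1 − ICC) × 0.5; residual e = (1 − ICC) × 0.5. A stable home effect cancels, because every home is surveyed in both waves.

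**True variance divided by the variance the test assumes.**
- Unpaired: R = m·b + c(1 − f) + e
- Paired: R = (m·b + e)/(b + e), with m counting paired staff only
- Type I error = 2 × [1 − Φ(1.96/√R)]

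**Middle case** (m = 40, ICC 0.05, CAC 0.8, f = 0.5): b = 0.01 and c = e = 0.475.
- Unpaired: R = 0.40 + 0.2375 + 0.475 = 1.11, type I error 6.3%.
- Paired, on the 20 staff per home who answer twice: R = (0.20 + 0.475)/0.485 = 1.39, type I error 9.7%.

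| Scenario | Test | R | Formula | Simulated (4,000 trials) |
|---|---|---|---|---|
| m 40, ICC 0.10, CAC 1, all answer twice | unpaired | 0.45 | 0.3% | not run |
| m 40, ICC 0.05, CAC 1, all answer twice | unpaired | 0.47 | 0.4% | 0.5% |
| the same | paired | 1.00 | 5.0% | 4.8% |
| middle case | unpaired | 1.11 | 6.3% | 6.1% |
| middle case, retained staff | paired | 1.39 | 9.7% | 10.7% |
| m 60, ICC 0.10, CAC 0.5, none answer twice | unpaired | 3.90 | 32% | 32% |
| m 60, ICC 0.10, CAC 0.5, all answer twice | paired | 6.90 | 46% | not run |

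A paired *t*-test on the 12 home means gave 4.3% to 5.3% in all simulated scenarios without drift.

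**Drift.** With baselines at months 0 to 11 and follow-up at month 13, the lag runs from 13 down to 2 months, mean 7.5. A drift of 0.02 SD per month gives a spurious change of 7.5 × 0.02 = 0.15 SD. In the middle case the true SE is √[(2/12)(0.01 + 0.7125/40)] = 0.0681. The unpaired test assumes √[2/(12 × 40)] = 0.0645 and rejects beyond 1.96 × 0.0645 = 0.126. The chance of rejecting is Φ[(0.15 − 0.126)/0.0681], about 0.635. Simulated with no programme effect:

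| Drift (SD per month) | Unpaired | Paired | 12 home means |
|---|---|---|---|
| 0.01 | 20% | 25% | 16% |
| 0.02 | 63% | 62% | 48% |
| 0.03 | 93% | 92% | 79% |

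**Can calendar time be adjusted for?** With month as a category, the design matrix has 14 columns and rank 13, so the phase effect is not estimable. With month as a linear term, the SE in the middle case rises from 0.068 to 0.150 SD and the difference detectable with 80% power from 0.19 to 0.42 SD. Over four scenarios the SE rose 2.0 to 2.25 times.

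**The case against.** **The test may be paired.** A reader might infer that the plan ignores repeated staff. The article never says unpaired, and the further regression on change hints that responses are linked. The analysis plan, not shown, may settle it. This stands: the fair point is that the article leaves pairing open. Pairing alone does not deal with home-by-wave variation or with drift.

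**The p-value need not be badly wrong.** This also stands. Stable home effects cancel; if home effects are fully stable, a paired test is correct, and in the middle case the unpaired test is close to nominal. A reader might go further and quote an unpaired SE 41% too wide (1/√(1 − 0.5) = 1.41) together with a false-positive rate of 10% to 25% (design effects 1 + 19 × 0.02 = 1.38 and 1 + 39 × 0.05 = 2.95). The two figures cannot be joined: the first assumes that all staff answer twice with no clustering, the second clustering with no repeated staff. With all staff paired, overall correlation 0.5 and the same home-by-wave values, R = 0.40 + 0.48 = 0.88 (3.7%) to 2.00 + 0.45 = 2.45 (21%).

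**The regression may include the home.** True, but it covers one of the two scales, includes the home only optionally, is aimed at staff-related factors and has no time term. It does not repair the test.

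**No causal claim is made.** The Outcome 6 text promises only a before-after change. That is fair, though Table 1 places the outcome under effectiveness, so the limit should be stated.

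**A calendar-month term would allow attribution.** A reader might infer this from the staggered baselines. The survey dates do not support it: the effect is not estimable with month as a category. A linear term rests on linear drift and a constant programme effect, since within a home the lag also measures time since the programme began.

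**Conclusion.** The point holds in a limited form. The test named for Outcome 6 leaves pairing unstated and has no home term, in contrast with Outcomes 1 to 4. Its error rate at a nominal 5% could lie anywhere from under 1% to above 30%, with about 6% (unpaired) to 11% (paired) in the middle case. These sizes rest wholly on the assumed staff numbers, correlations and retention; the article supplies none of them, so neither the direction nor the size of the error is established for this trial.

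The limit on interpretation is firmer, because it follows from the survey dates (provided that exposure ends together in all homes): whichever *t*-test is meant, the result is an uncontrolled before-after change. Outcome 6 is secondary, and the primary analysis is unaffected.

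**What to change.** 1. For both the job-related and the group-related scale, replace the *t*-test with a linear mixed model: phase (before or after), a random intercept for home, a random intercept for staff member where responses can be linked, and a random home-by-phase term. Use all responses and report the phase difference with a small-sample (Kenward-Roger) interval. A paired *t*-test on the 12 home means is a simple equivalent and needs no linking of individuals.
2. State whether individual responses can be linked between the two surveys.
3. Report the result as an uncontrolled before-after change, not as an effect of EDDIE+.
4. If wanted, add a linear calendar-month term as a sensitivity analysis only, noting that it about doubles the standard error and relies on linear drift and a constant programme effect.

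**Cost.** Wording and code, plus an anonymous linking code on the questionnaire if there is none. The interval is somewhat wider: in the middle case, analysing the 12 home means (t critical value 2.20 on 11 degrees of freedom) gives a half-width of 2.20 × 0.0681 = 0.150 SD, against 1.96 × 0.0645 = 0.126 SD for the unpaired test, about 19% more. The conclusion is more modest. No change to survey dates is needed unless attribution to the programme is wanted; that would require surveys during the roll-out in homes not yet switched.
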